### Ethical considerations

Written consent will be obtained from all family caregivers in accordance with regulations.

The study protocol has been reviewed and approved by the Ethics Committee of ICS Maugeri Institute (prot. n. 345). The study will be conducted in accordance with the principles of the Declaration of Helsinki. Moreover, the protocol has been registered (Clinicaltrial.gov NCT05706831). Any changes to the protocol will be submitted to the ethics committee for approval.

Each patient entering the project will be assigned with a unique identifier and the code for linking private information to the identifier is securely stored at the Clinic. Identifiable information is restricted to authorised investigators from Maugeri Clinic. All outcome data are anonymised right after acquisition and then transferred to a password-protected folder on a server.

This protocol is a part of a more extended randomized cross-over intervention trial which includes also stroke patients stratified in patients with post-stroke aphasia and patients with post-stroke neglect. In this protocol paper, we focus only on patients with DOC.

### Sample size determination

The effect size to be expected is uncertain as no study so far has implemented a combined intervention of music and electrical stimulation in DOC patients. We assume it to be in the medium-to large range (i.e., Cohen’s d between 0.5 and 0.8). We aim to achieve 80% power (*f* = 0.30) in a repeated-measures analysis of variance (*a* = 0.05, power (1-b) = 0.80) with condition as between-subject factor (tES combined with music stimulation vs. sham stimulation, and noise vs. music stimulation and sham stimulation), and time (pre-intervention, post-intervention and post-placebo), as within-subject factor. Power calculations (using G* Power 3) indicate that a valid sample size of *n* = 10 per group will result in 80% statistical power if the effect is *d* = 0.68, which is in the medium-to-large range. This results in a total sample size of *n* = 30.

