**Methods:**

This is a randomised cross-over trial in which a total of 30 participants will be randomly allocated to one of three different combinations of conditions: (i) Music only, (ii) tES only (control condition), (iii) Music + tES. The music intervention will consist of listening to an individually tailored playlist including familiar and self-relevant music together with fixed songs; concerning NIBS, tES will be applied for 20 minutes every day, 5 times a week, for two weeks. After these stimulations two weeks of placebo treatments will follow, with sham stimulation combined with noise for other two weeks. The primary outcomes will be clinical, i.e., based on the differences in the scores obtained on the neuropsychological tests, such as Coma Recovery Scale-Revised, and neurophysiological measures as EEG, collected pre-intervention, post-intervention and post-placebo.

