**Fig 1 pone.0304642.g001:**
[figure not shown]
Study flow diagram displaying interventions and assessments.

For the treatment condition, music stimulation, lasting overall around 30 minutes, will be provided by headphones for two weeks in a row every day (except weekends) twice a day: in the morning and in the afternoon. In the morning only, this music-listening treatment will be preceded by brain stimulation with tES applied in the hemisphere contralateral to the lesion (position of electrodes adjusted according to clinical condition of the patient). The placebo condition will have the same temporal course of the treatment condition, but, instead of music, patients will listen to white noise for 30 minutes in the morning, and pink noise for 30 minutes in the afternoon and only during the morning sessions, sham (current induction for 10 minutes ramp up and 10 minutes ramp down) in the hemisphere contralateral to the lesion will be delivered. Between the two conditions, one week of washout is planned.

Patients who will develop relevant clinical condition, such as respiratory problems, during the period of protocol, will be excluded from the study.

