### Data analysis

The SPSS 23.0 statistical software will be used for the data analysis. All the statistical hypotheses will be tested by two-side test, with statistically significant test level set at 0.05 and the confidence interval estimation to 95%.

The aim of our study is to evaluate the effects of the treatments in the various patient groups on the primary and secondary outcomes. Descriptive analysis of the data will allow us to identify the characteristics of the groups. Comparison of demographic and clinical characteristics of the groups will be performed using one-way ANOVA for continuous variables and the Chi-square test for categorical variables. Considering the crossover and longitudinal aspects, primary analyses will focus on behavioural changes at group level, comparing the treatments. Moreover, at the individual level, we will analyse the differences between pre-treatments and post treatments data.

As for the primary outcomes, we will measure the effects of the intervention on the following measures (two neurophysiological and two clinical and behavioral): (i) power spectra of frequency band extracted from the EEG recordings; (ii) auditory evoked responses, extracted from the EEG recordings; (iii) behavioural responses of DOC patients, measured through CRS-R.

Baseline characteristics and carryover effect will be analysed between the three sequences using ANOVA and chi-square test. By including the order of intervention as a covariate, we aim to determine whether the sequence in which participants receive the interventions impacts the observed outcomes. To assess the presence and magnitude of the washout effect, we plan to incorporate appropriate statistical methods into our analysis, such as comparing outcomes during the washout period to those observed during active treatment phases. To this end, we will use repeated measures ANOVA considering time (before, during, and after the washout) as the independent variable, with behavioral measurements as the dependent variables.

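### The 30 valid patients behind the 80% power figure are the same 30 who are randomised, so the protocol's own exclusion rule breaks the stated sample at the first loss

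*Protocol article*

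**What the plan says.** Four places in the protocol article bear on this.

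- **Sample size determination.** The power statement refers to evaluable patients: the calculations "indicate that a valid sample size of" 10 per group reach 80% power. The total of 30 follows directly ("This results in a total sample size of" 30), which is 3 × 10 with nothing added. The test is a repeated-measures ANOVA ("We aim to achieve 80% power (*f* = 0.30) in a repeated-measures analysis of variance") with alpha 0.05 and three levels of time: before the intervention, after it, and after placebo.
- **Abstract, Methods.** The same 30 is the number entering the trial: "a total of 30 participants will be randomly allocated".
- **Experimental design and procedures.** The schedule is two weeks, one week of washout and two more weeks. Patients who develop a relevant clinical condition "during the period of protocol, will be excluded from the study"; respiratory problems are the example given.
- **Discussion, limitations.** A larger sample will be considered if preliminary analyses show an effect clearly smaller than predicted. Losses are not a trigger.

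**The concern.** Power is claimed for patients who can be analysed, while the enrolment figure counts patients who are randomised. The two are set equal in a protocol that itself provides for removing patients after the start. A reader who takes the section at its word will expect 30 evaluable patients and 80% power, and the Discussion names the sample size as a strength. Once the exclusion rule is used, the design no longer delivers the stated sample. How far power then falls depends on settings that the article does not give.

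**Working it through.** **Head count.** Valid sample required: 3 × 10 = 30. Randomised: 30. Margin: 30 − 30 = 0. One exclusion leaves 29, with 9 in one group.

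**How likely it is that all 30 remain.** The article gives no loss rate, so this is an assumption. With an independent 5% risk of exclusion per patient, the probability is 0.95^30 = 0.21. At 10% it is 0.90^30 = 0.04.

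**Inputs for power.**
- From Sample size determination: f = 0.30, alpha 0.05, target power 0.80, three time points.
- Number of groups k = 3 (10 per group, 30 in total).
- Not stated, and so assumed: the correlation between repeated measures (rho), sphericity, and that the powered effect is the group-by-time interaction.

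**Formula** (within-between interaction, noncentral F):
- noncentrality = f² × N × m / (1 − rho)
- df1 = (k − 1)(m − 1)
- df2 = (N − k)(m − 1)

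Here m is the number of measurements.

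**Reproducing N = 30.** Two settings do so.
- m = 2, rho = 0.5: noncentrality = 0.09 × 30 × 2 / 0.5 = 10.8, df 2 and 27, power 0.800.
- m = 3: solving for power 0.80 at N = 30 gives rho of about 0.38. Noncentrality = 0.09 × 30 × 3 / 0.62 = 13.1, df 4 and 54, power 0.80.

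The first setting has one measurement fewer than the section names. The second uses the three time points as stated.

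**The stated time points with rho = 0.5.** Noncentrality = 0.09 × 30 × 3 / 0.5 = 16.2, df 4 and 54, power 0.887. This setting does not reproduce 80% at 30; it reaches 80% from N = 25.

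**Power after losses:**

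| Evaluable N | m = 2, rho 0.5 | m = 3, rho 0.38 | m = 3, rho 0.5 |
|---|---|---|---|
| 30 | 80.0% | 80% | 88.7% |
| 29 | 78.4% | 78.4% | 87.4% |
| 27 (10% loss) | 74.8% | 74.7% | 84.4% |
| 25 | 70.8% | 70.5% | 80.7% |
| 24 (20% loss) | 68.6% | 68.2% | 78.6% |

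The first two columns nearly coincide. Once 80% at 30 is accepted, the number of measurements hardly alters what the losses cost.

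**Effect size.** The section also gives d = 0.68. If f = d/2, that is f = 0.34, not 0.30. This is a second reason why the settings cannot be recovered from the text.

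**The case against.** The strongest reply is that the shortfall in power depends on the chosen setting. The protocol names three time points. With rho = 0.5 that gives 88.7% at 30, and the trial could lose five patients before falling below 80%. This stands. A reader might infer that the design has no slack in power, or that power drops below 80% whichever comparison the figure describes. The document supports neither, because it states no correlation. What is established is conditional: in any of these settings where 80% at 30 is true, one loss takes power below 80%. Where there is slack, the statement that 10 per group give 80% misreports the calculation.

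A second reply is that a condensed article may leave replacement of patients to the full protocol, and that exclusion from the study need not mean discarding data already collected. The Data analysis section does provide for missing data, by citation. This also has weight: the point should not rest on silence about replacement, and it cannot be settled whether a partly observed patient would count as valid. But the valid number, the randomised number and the exclusion rule are all printed, and they do not fit together as printed. A method for missing data does not make an excluded patient one of 30 complete ones.

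Third, one exclusion costs only about 1.6 percentage points (80.0% to 78.4%). That is correct, and a reader should not take this as a collapse of power.

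**Conclusion.** The concern holds as a mismatch of head counts. The article promises 30 valid patients, randomises 30 and plans to exclude some, so the stated sample is missed at the first exclusion. That conclusion needs no assumption about the power model.

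The effect on power is moderate and conditional. If 80% at 30 is correct, power is about 78% at 29, 75% at 27 and 68–69% at 24. With three time points and correlation 0.5 it is 87.4%, 84.4% and 78.6%, and the stated 80% is then itself wrong. The loss rates and correlations are assumptions, since the article gives neither. The figures of 75% and 69% are therefore illustrations and should not be printed as this trial's power. The correction is worth making, but it does not call the design into question.

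**What to change.** In Sample size determination:

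1. Say that 30 is the number randomised, and drop the word *valid* for that figure.
2. State the evaluable number expected after exclusions, with the assumed loss rate and its basis.
3. Report power at that number from the settings actually used: three time points, a stated correlation, the effect tested, and one effect size in place of both f = 0.30 and d = 0.68.
4. If the correlation is uncertain, give power over a range of values.

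The cost is a rerun of the power calculation and a few sentences. Enrolment and the exclusion rule can stay as they are. The downside is that the stated power may be somewhat less favourable. If the sponsor would rather keep 30 evaluable patients, 30 / (1 − loss) gives 34 randomised at 10% loss and 38 at 20% (36 and 39 with equal groups). That is a separate choice and is not needed to correct the statement.

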
With this study we propose a novel rehabilitation protocol that combines music-based intervention and NIBS in neurological patients aimed to (i) assess the residual neuroplastic processes existing in DOC state, and (ii) evaluate the putative modulation of these processes by a non-pharmacological 2-weeks intervention combining electric (tES) and auditory (music) stimulation. The musical stimulation will consist of musical pieces that vary in familiarity and complexity (from pieces chosen from the favourite ones for the patient to novel pieces following classical tonal style up to atonal pieces). We hypothesize that tES, altering the physiology of neural circuits, can increase the plastic effect of music stimulation and thus increase the responsiveness of the patient. As far as we know, there are no studies in the literature that have evaluated the effectiveness of the association of these treatments in DOC patients Furthermore, an additional novel aspect will be the use of autobiographical music, hence emotionally relevant to the patients.

In addition, we also want to ascertain the influence of this rehabilitation protocol on caregiver’s burden and psychological distress, since acquired brain injury has an important impact on physical, psychological, social and also financial conditions of caregivers; their entire life is modified in order to take care of the patient, causing a strong emotional burden, with high levels of psychophysiological distress, depression, anxiety and a more complex symptomatology called prolonged grief disorders [43, 44]. In this regard, an aim of this study is to evaluate the caregiver’s psychological burden both before and post rehabilitation treatment in order to assess the effect of music stimulation and brain stimulation also on caregiver’s emotional condition.

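### The power statement is internally inconsistent, and 10 patients per group do not give 80% power at d = 0.68 for between-group contrasts such as combined treatment versus music

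*Protocol article*

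**What the plan says.** All of this is in the protocol article.

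- **Sample size determination** sets the target: "We aim to achieve 80% power (*f* = 0.30) in a repeated-measures analysis of variance". The model is described as "with condition as between-subject factor (tES combined with music stimulation vs. sham stimulation, and noise vs. music stimulation and sham stimulation"), with time at three levels as the within-subject factor. The result is that "10 per group will result in 80% statistical power if the effect is" d = 0.68, with 30 in total. The section does not say whether the powered effect is condition, time or their interaction, and it gives no correlation between repeated measurements.
- **Data analysis** fixes the error rate: "All the statistical hypotheses will be tested by two-side test", "with statistically significant test level set at 0.05".
- **Introduction** gives the scientific hypothesis, that tES "can increase the plastic effect of music stimulation and thus increase the responsiveness of the patient".
- **Experimental design and procedures** defines three randomised sequences: combined then placebo, placebo then combined, and music then placebo. Placebo is sham stimulation with noise.

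**The concern.** Two effect sizes, f = 0.30 and d = 0.68, carry the same 80%, but nothing shows that they describe the same effect. Most readers will take d = 0.68 with 10 per group as a standardised difference between two groups of 10, and 80% is far too high for that.

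The contrast that tests the Introduction's hypothesis is combined treatment against music alone. Under the three sequences no patient receives both, so it is a comparison between patients. If it came out null, readers would set that result against a stated 80% power. The Discussion also lists the sample size among the study's strengths, and it ties a possible extension to the effect falling short of the predicted size. The prediction therefore has to be stated correctly.

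**Working it through.** **Inputs from the article:** two-sided alpha 0.05, N = 30, k = 3 groups of 10, f = 0.30, d = 0.68, three assessment times. **Assumed, because not stated:** correlation rho between measurements of 0.5, range 0.3 to 0.7; sphericity; no loss. Power is from the noncentral F or t distribution, and m is the number of measurements.

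**1. Reproducing 80% at N = 30.** For the group-by-time interaction, lambda = f² × N × m / (1 − rho), with df (k − 1)(m − 1) and (N − k)(m − 1).
- m = 2, f = 0.30, rho = 0.5: lambda = 0.09 × 30 × 2 / 0.5 = 10.8, df 2 and 27, power 80.0%. With N = 29 it is 78.4%. This matches the article's figures.
- m = 3, as the article lists: lambda = 0.09 × 30 × 3 / 0.5 = 16.2, df 4 and 54, power 88.7%.
- m = 3 with f = 0.34 (d = 0.68 under d = 2f): lambda = 0.1156 × 90 / 0.5 = 20.8, power 95.5%.
- With m = 3, 80% is reached only at a correlation of about 0.38 (f = 0.30) or 0.20 (f = 0.34), and the article states neither.

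**2. What f = 0.30 means in that test.** With two measurements the interaction f is half the standard deviation of the three mean changes, in outcome SD units. If the largest difference in change is D, that standard deviation is 0.408 D when the groups are evenly spaced and 0.471 D when one group stands apart.
- f = 0.30 gives D = 0.60 / 0.408 = 1.47 SD, or 0.60 / 0.471 = 1.27 SD.
- Conversely, D = 0.68 gives f = 0.68 × 0.408 / 2 = 0.139, or 0.68 × 0.471 / 2 = 0.160.

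On the simple rule d = 2f, f = 0.30 would be d = 0.60, which is not 0.68 either.

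**3. Power for a between-group difference of 0.68 SD.**

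| Test | Formula | rho 0.3 | rho 0.5 | rho 0.7 |
|---|---|---|---|---|
| 10 v 10 t test, one time point | 0.68 × √(10/2) = 1.52, df 18 | 30% | 30% | 30% |
| 10 v 10, adjusted for T0 | 1.52 / √(1 − rho²) = 1.59, 1.76, 2.13 | 32% | 38% | 52% |
| Three-group test of change, f = 0.139 | lambda = f² × 60 / (1 − rho) | 18% | 23% | 36% |
| Three-group test of change, f = 0.160 | same | 22% | 30% | 47% |
| 3 × 3 interaction, one group 0.68 higher at one time, f = 0.68 × 2/9 = 0.151 | lambda = f² × 90 / (1 − rho) | 22% | 30% | 49% |

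**4. Condition as a between-subject main effect over three times.** lambda = f² × N × m / (1 + (m − 1) rho), df 2 and 27. At rho = 0.5, f = 0.30 gives 8.1 / 2 = 4.05 and power 38%; f = 0.34 gives 10.4 / 2 = 5.2 and power 47%. Even at rho = 0 and f = 0.34 it is 78.5%.

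**5. What 80% would need for 10 v 10.** The unadjusted detectable effect is d of about 1.32; at d = 0.68 about 35 per group would be needed. Adjustment for T0 multiplies the detectable d by roughly √(1 − rho²): 1.32 × 0.954 = 1.26, 1.32 × 0.866 = 1.14 and 1.32 × 0.714 = 0.94 at rho 0.3, 0.5 and 0.7.

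**6. Within-patient contrast, for comparison.** Combined versus placebo in the 20 patients who receive both in randomised order: 0.68 × √20 / √(2(1 − rho)) = 2.57, 3.04 and 3.93, df 19, giving 68%, 82% and 96% at rho 0.3, 0.5 and 0.7, if there is no carryover and no loss.

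**The case against.** The strongest reply is that the article never says the 80% belongs to a between-subject comparison. It names a mixed repeated-measures ANOVA, and the interaction in that model does give 80.0% at N = 30. This stands: a reader might infer that the 80% is simply a false figure for the condition main effect, and the text does not support that. The calculation is under-specified. The number of measurements also errs in the safe direction, since three would give 88.7% at the same f and correlation.

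A reader might also infer that sham with noise cannot be a between-subject level because every patient receives it. That goes too far. In the first period the three groups receive combined treatment, placebo and music with sham, so from T0 to T1 they are three parallel conditions, and two measurements would suit that comparison.

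Nor can the shortfall be put at one narrow figure, because every value depends on a correlation the article does not give. The crossover helps some tests. If both combined sequences gain 0.68 SD in their active period, the 3 × 3 interaction has f = 0.239 and power of 52%, 69% and 91% at rho 0.3, 0.5 and 0.7. But that omnibus test does not isolate combined versus music.

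Finally, the article calls the effect size uncertain, admits possible overestimation and foresees an extension. That candour concerns the size of the true effect. It does not repair the link between 80% and d = 0.68.

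**Conclusion.** The power statement needs correcting. It is internally inconsistent: the tested effect and the correlation are missing, the measurements listed do not match those that return 80% at a correlation of 0.5, and f = 0.30 and d = 0.68 are offered as one effect when in the reproducing test they differ by about a factor of two (1.27 to 1.47 SD against 0.68 SD). For between-group contrasts, 80% at d = 0.68 with 10 per group is not delivered at any correlation from 0.3 to 0.7 in the tests of section 3 of the working, where power runs from 18% to 52%. The consequence falls mainly on combined versus music. The ranges assume sphericity and no loss. They do not show that the trial lacks power for every contrast, since combined versus placebo within patients may reach or exceed 80% if the correlation is about 0.5 or more and there is no carryover.

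**What to change.** Rewrite the sample size paragraph:

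- Name the powered effect, the number of measurements it uses, the assumed correlation and a single effect size, defined in terms of the group means or changes it describes.
- Remove the claim of 80% power at d = 0.68 for between-group contrasts.
- Give the power or the detectable effect for combined versus music: about d = 1.3 for 80% with 10 v 10 unadjusted, or the T0-adjusted value with its correlation.
- If a within-patient figure is quoted for combined versus placebo in the 20 two-way crossover patients, give it as a range over the correlation (68%, 82% and 96% at 0.3, 0.5 and 0.7) and state that it assumes no carryover and no loss.

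The cost is text only. No extra patients are needed; the price is a less favourable stated power for the combined-versus-music comparison.

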### Intervention

#### Brain stimulation

tES will be applied for 20 minutes every day, once a day, 5 times a week, for 2 weeks. During the first week, patients will be administered the real (*verum*) stimulation, while in the other week *sham* will be administered (the administration order will be counterbalanced across participants). Position of electrodes will be adjusted according to the clinical condition of the patient. In the *verum* condition, a direct current of 2 mA (anodal tDCS) will be delivered through a BrainStim battery driven electric stimulator in the target area of the brain, with the cathode on the contralateral arm. In the sham condition, the anode will deliver the direct current only for the first 20 sec. (i.e., 20 sec. rump-up).

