### Experimental design and procedures

The experimental paradigm is one of the main strengths of the study, as a randomized cross-over design will be used in this trial, including a treatment condition with electric brain stimulation combined with music listening and a placebo condition with sham brain stimulation combined with noise listening. The randomization of the participants to be included in each group will be done using the software “Research Randomizer” (www.randomizer.org). The randomization procedure will be performed by an independent researcher unrelated to the study. The randomization file will be saved in a password-protected online database. This independent researcher will enrol participants and will assign the patients to intervention groups. Both patients and examiner will be fully blinded.

Assessment times of outcome measures will be conducted at admission (T_0_), after the first weeks of post-intervention or post-placebo (T_1_), and after the second two weeks of post-intervention or post-placebo (T_2_) (Fig 1). Patients will be randomized into three groups depending on the order of the stimulation or placebo conditions:

Stimulation-Placebo: Patients receiving tES combined with music stimulation for 2 weeks, 1 week of wash out, then sham stimulation combined with noise (placebo) for other 2 weeks.Placebo-stimulation (combined tES and music): Patients receiving sham stimulation and noise (placebo) for the first 2 weeks, then 1 week wash out, and finally tES and music stimulation for other 2 weeks.Music-placebo: Patients receiving music stimulation and sham stimulation for 2 weeks, 1 week of wash out, then sham stimulation and noise (placebo) for another 2 weeks.

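### Sham tES is specified in two incompatible ways, 20 seconds of current or 20 minutes of ramping, and the second taken literally makes the placebo partly active

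*Protocol article*

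**What the plan says.** **Sham, first definition.** The Brain stimulation section sets verum at 2 mA anodal tDCS, 20 minutes once a day, five days a week for two weeks. It then says of sham: "In the sham condition, the anode will deliver the direct current only for the first 20 sec", adding that this is a 20-second ramp-up.

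**Sham, second definition.** Under Experimental design and procedures, in the text after Fig 1, the morning placebo session is said to use "sham (current induction for 10 minutes ramp up and 10 minutes ramp down) in the hemisphere contralateral to the lesion will be delivered".

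**Where sham is used.** Sham with noise is the placebo block in all three sequences. Sham also accompanies music in the third sequence ("Patients receiving music stimulation and sham stimulation for 2 weeks"), where its settings are not described.

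**Length of the active course.** The Brain stimulation section also says "During the first week, patients will be administered the real" stimulation and the other week sham, with the order counterbalanced. Elsewhere the active block is two weeks. The Abstract (Methods) has "tES will be applied for 20 minutes every day, 5 times a week, for two weeks", followed by a separate two-week placebo period. Experimental design and procedures has "Patients receiving tES combined with music stimulation for 2 weeks, 1 week of wash out", and only after that washout the sham and noise block.

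**The concern.** Sham is the control for the electrical component, so its definition fixes the dose in the comparator. The two descriptions cannot both be true: one switches the current off after 20 seconds, the other keeps it on for the full session. Every patient has a placebo block, so every patient is affected by the choice.

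If the long version is programmed as written, placebo patients receive current throughout each of ten sessions, and the contrast between combined treatment and placebo is diluted. The contrast between combined treatment and music alone would be affected as well, but only if the same sham is used in the music block. The Introduction describes tES as a 1 to 2 mA current whose after-effects become more stable with repetition, so on the protocol's own account ten sessions of slow ramping to such a level could not be assumed inert. No analysis could undo this afterwards.

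The week-by-week sentence puts the other side of the contrast in doubt: followed literally, it halves the number of active sessions and places sham inside the active block.

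**Working it through.** The plan gives no charge figure to reproduce, so the check compares delivered charge (current × time) under each reading.

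**Inputs from the article**
- Verum: 2 mA, 20 min = 1,200 s (Brain stimulation).
- Short sham: current for 20 s (Brain stimulation).
- Long sham: 10 min up + 10 min down = 1,200 s (text after Fig 1).
- Sessions per two-week block: 5 × 2 = 10.

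**Assumptions**
- Ramps are linear, so charge = 0.5 × peak × total ramp time.
- The sham peak is not stated. The main range is 1 to 2 mA, with 0.5 mA shown as a lower case.
- Verum is taken at 2 mA for the whole session.

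**Per session**

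| Reading | Calculation | Charge | Share of verum |
|---|---|---|---|
| Verum | 0.002 A × 1,200 s | 2.4 C | 100% |
| Long sham, peak 2 mA | 0.5 × 0.002 × 1,200 | 1.2 C | 50% |
| Long sham, peak 1 mA | 0.5 × 0.001 × 1,200 | 0.6 C | 25% |
| Long sham, peak 0.5 mA | 0.5 × 0.0005 × 1,200 | 0.3 C | 12.5% |
| Short sham, constant 2 mA (upper bound) | 0.002 × 20 | 0.04 C | 1.7% |
| Short sham, 20 s ramp to 2 mA | 0.5 × 0.002 × 20 | 0.02 C | 0.8% |
| Long sham if minutes means seconds, peak 2 mA | 0.5 × 0.002 × 20 | 0.02 C | 0.8% |

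**Duration.** 1,200 s ÷ 20 s = 60-fold difference in time with current on. With a 2 mA peak, the long sham reaches 1 mA at minute 5 and falls below it at minute 15, so it is at or above 1 mA for the middle 10 minutes.

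**Verum minus sham.** Long sham with a 1 to 2 mA peak: 100% − 25% = 75%, down to 100% − 50% = 50% of the verum charge. Short sham: at least 100% − 1.7% = 98.3%.

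**Over ten sessions.** Verum 24 C; long sham 6 to 12 C; short sham at most 0.4 C.

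**Active sessions per tES block.** Two weeks of verum: 2 × 5 = 10. One verum week and one sham week: 1 × 5 = 5, that is 12 C of verum charge in place of 24 C.

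**The case against.** The strongest reply is that this is a unit slip. Ten plus ten is twenty, the figure the Brain stimulation section gives in seconds. That section is the dedicated description of the stimulation, the other is a parenthesis in a procedures paragraph, and a ramp lasting the whole session would defeat the purpose of a condition labelled placebo. This is a plausible explanation, and if it is right the dose conflict disappears. It is not established, however. The 10 + 10 minutes also fit the 20-minute session exactly, so the figure would not look wrong to someone setting the device. Even 10 s up and 10 s down does not fully match a description that mentions only a 20-second ramp-up.

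Second, the percentages rest on an assumed peak current and ramp shape, and charge is not clinical effect. This stands. The article gives no dose-response, so the charge shares cannot be turned into a loss of effect size or power. What does not depend on the assumptions is 20 seconds against 20 minutes of non-zero current.

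Third, the article condenses an ethics-approved protocol that is not shown and may be clear on the setting. That affects which document needs correcting, but the article still states the parameter twice, differently.

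Fourth, the week-split sentence is a separate inconsistency about schedule. That is fair, and it is treated here as secondary. References to a two-week intervention do not by themselves contradict it, since the same section says two weeks before splitting them. The conflict is with the sequences, which put sham in its own two-week block after the washout, and with the Abstract's separate placebo period.

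**Conclusion.** The concern holds. The two sham definitions are both current text, apply to the same control condition, differ 60-fold in time with current on, and are not reconciled. Read literally, the longer one gives a placebo carrying 25% to 50% of the verum charge per session if ramps are linear and the peak is 1 to 2 mA (12.5% at 0.5 mA), against at most 1.7% for the shorter one. Confidence is high that the contradiction exists. Whether any placebo was or will be partly active depends on which setting is programmed, and the article cannot answer that. The effect on combined treatment versus music depends further on whether the music block uses the same sham. The schedule sentence is a real but secondary conflict, 5 versus 10 active sessions per tES block. Because the sham setting determines the comparator dose for every patient, this must be fixed even if it proves to be a slip.

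**What to change.** 1. Replace the sham description after Fig 1 with the brief sham of the Brain stimulation section, and complete it in both places: peak current, ramp-up and ramp-down in seconds (about 20 s of current in total), and zero current for the rest of the 20 minutes.
2. State that this same sham applies in every placebo block and in the music block.
3. Replace the sentence splitting the course into a verum and a sham week with two weeks (10 sessions) of verum per tES block, and let order vary only through the randomised sequences.
4. Check the sham programme on the stimulator, and record which version, and how many verum sessions, any patient already treated received.

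Cost: two sentence corrections submitted to the ethics committee and a check of device settings. If the approved full protocol already has the right wording, only the article needs correcting. No new patients, visits or procedures are required.
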